### Intervention schools

2.6

Multicomponent interventions will be offered, including 5 identical 2-hour education sessions to adolescents and parents/guardians in each school (28 adolescents and 28 parents/guardians in each session). The project nurse will assume the role of “HPV immunization advisor” and pair with healthcare and lay volunteers to facilitate small-group discussions, encouraging engagement, and dialogue. The topics introduced in these identical sessions will include the mechanism of spread of HPV; diseases or conditions caused by HPV; HPV prevention; incidence of cervical cancer, its symptoms and complications, high-risk groups, and prevention; efficacy and safety of HPV vaccines; recommendations and duration of protection by HPV vaccine; concept of herd immunity; benefit–risk ratios; common misconceptions and concerns; and concerns about costs, safety, and side effects of vaccines. The education sessions will be offered after school hours, including evenings and weekends to fit the schedules of working parents/guardians. Online educational computer games will also be introduced to adolescents. These games will encourage adolescents to learn about the concept of vaccination as an effective preventive measure against HPV, resolve common misconceptions, and provide justifications for HPV vaccination.

To assure program sustainability, a 2-hour education session will be offered to school personnel, including teachers, school nurses, social workers, and administrative staff. All teaching and learning materials will be rigorously reviewed by a multidisciplinary team of nurse consultants, nurse academics, physicians, pharmacists, and infectious disease specialists to ensure content validity. A pilot study of 3 health education sessions will be conducted with 9 participants (including adolescents, parents/guardians, and teachers). Participants will be asked to comment on the acceptability and feasibility of the education sessions and pre-test the instruments to identify issues related to data collection. Five 3-hour training sessions lead by 4 experts in pediatric nursing, public health, pharmacology, and infectious diseases will be provided to build upon project nurses’ skills and experience in delivering the intervention. Topics will include therapeutic communication skills with adolescents, parents/guardians and teachers; vaccine pharmacology; HPV infection and prevention; empowerment of parents/guardians and adolescents to make healthy decisions; and the innovative application of computer games in healthcare decisions.

Regarding capacity building, we will establish a core team of volunteers, including 30 healthcare volunteers (physicians, registered nurses, pharmacists, and social workers) and 120 lay volunteers (university students), to assist in the education sessions (at least 1 healthcare and 3 lay volunteers per session). All volunteers will attend a 2-day training session conducted by the project team on health education and promotion theories; communication skills; knowledge about cervical cancer; HPV; and HPV vaccination. Ten video-based scenarios about strategies to engage adolescents and their parents/guardians in open dialogue (including good and poor practices) will be developed. Discussions, role-playing sessions, and adolescents and parents/guardians simulation practice will be conducted. A training manual will be developed to summarize the training contents. All volunteers must pass a quiz and perform satisfactorily in an encounter with 2 pairs of simulated participants of an adolescent and their parent/guardian. A certificate will be issued after completion of training.

### Control schools

2.7

Parents/guardians and adolescents from control schools will receive a 30-minute educational video on HPV, cervical cancer, and the HPV vaccine designed to enhance HPV vaccine acceptance. A video is provided to avoid exclusion of any parents/guardians who may be illiterate.

### Outcome measures

2.8

Outcomes will be determined 1 month after the intervention (i.e., the education sessions) (T1) and 1 year after the intervention (T2) and will be collected by a research assistant unaware of the group allocation. Adolescents and their parents/guardians will be asked to report their immunization status during the 1-year follow-up (T2).

#### Immunization status and intention

2.8.1

HPV vaccine uptake (when and where) as determined by the proportion of female adolescents vaccinated; and adolescents’ intention to vaccinate on a 10-point Likert scale (1 = definitely not, 10 = definitely)^[32]^ and reasons for no or low intention (a score <5) will be sought.

#### Parents/guardians’ acceptance of HPV vaccination

2.8.2

The 6 PAPM stages proposed by Shapiro et al^[33]^ will be used to identify the stage of parents/guardians’ HPV vaccine decision-making at baseline (T0) and T1. The 6 stages include unaware of the vaccine; unengaged in the decision to vaccinate their daughter; undecided; decided not to act; decided to act; and already acted (vaccinated their daughter). The PAPM is a stage-based theoretical model, aiding better understanding of the vaccine acceptance process among respondents.^[34]^

#### Parents/guardians’ and adolescents’ attitudes and beliefs regarding HPV vaccination

2.8.3

The 18-item Carolina HPV Immunization Attitudes and Beliefs Scale (CHIAS)^[34]^ based on HBM constructs will be used to measure parents/guardians’ attitudes and beliefs about the HPV vaccine. Participants will rate each item on a 4-point scale, with higher values denoting stronger agreement. An example of a statement in this scale is “The HPV vaccine might cause lasting health problems.” The CHIAS examined HPV vaccine decision-making and was validated in a group of 783 parents who had not vaccinated their daughters. The 4 CHIAS factors include “perceived vaccination harms,” “perceived barriers,” “perceived vaccine effectiveness,” and “uncertainty about the vaccine.” All factors have acceptable internal consistencies, with Cronbach alpha (*α*) values ranging from 0.61 to 0.69.^[34]^

The 17-item modified CHIAS^[35]^ will be used to measure adolescents’ attitudes and beliefs about the HPV vaccine. Participants will rate each item on an 11-point scale, with higher values denoting lower endorsement of HPV vaccination. The scale was validated in 139 college-aged women and yielded a factor structure similar to studies with parents. Three of the factors (barriers, harms, and effectiveness) show good internal consistency, with Cronbach *α* from 0.74 to 0.90, while the other 2 factors (uncertainty and risk denial) have Cronbach *α* of 0.43 to 0.49.^[35]^

#### Adolescents’ and parents’/guardians’ knowledge about HPV and HPV vaccine

2.8.4

A 23-item HPV knowledge scale (GK23) and a 9-item vaccination knowledge scale (VK9)^[36]^ will be used to measure adolescents’ and parents/guardians’ knowledge about HPV and the HPV vaccine. Participants will be asked to respond “true,” “false,” or “don’t know” to 32 items. Both scales have been validated and used in studies in which parents’ knowledge about HPV and the HPV vaccine was examined.^[36]^ The GK23 has high internal consistency, with a Cronbach *α* of 0.89. The Cronbach *α* of VK9 is 0.68.

All instruments will be translated into Chinese, blind back-translated, reviewed, and modified by independent bilingual persons. The translated instruments will be validated with a group of 100 female secondary school students and 100 parents. An online survey of these instruments will be conducted.

#### Socio-demographic and vaccination information

2.8.5

Information collected will comprise: parents/guardians’ age, sex, educational level, occupation, income, and current and past medical history; number of children in the family; adolescents’ age and immunization history; receipt of influenza and HPV vaccine, and educational talks on HPV vaccination; HPV immunization of family members; and whether vaccinations have been discussed with healthcare professionals.

### Data collection methods

2.9

Adolescents in both groups will be asked to complete the online surveys at 3 time points: T0, after receiving parental and adolescent consent; T1, 1 month after the program (T0 and T1 will assess both adolescents’ intention to receive HPV vaccine and HPV knowledge, attitudes, and beliefs); and T2, 1 year after the program, at which time we will collect information about adolescents’ uptake of the HPV vaccine. Telephone or online surveys will be administered to parents/guardians in both groups at the same time points: at T0 and T1, to assess vaccine acceptance among parents/guardians and their HPV knowledge, attitudes and beliefs; and at T2, to collect information about the uptake of HPV vaccine among their daughters. In addition, satisfaction data from adolescents, parents/guardians, and teachers of both groups will be collected at T1 (via online survey for adolescents, and telephone or online survey for parents/guardians and teachers). Feedback from project nurse and volunteers will be collected at T1 (via telephone interviews). Research assistant, who will collect the study outcome data (except the satisfaction data for both groups collected by another research assistant) and perform data entry and analysis will remain blinded to the treatment allocation.

### Data analysis

2.10

Data will be summarized and presented using appropriate descriptive statistics. The normality of continuous variables will be assessed using skewness and kurtosis statistics and a normal probability plot. Suitable transformations will be made on skewed variables before subjecting them to inferential analysis, if necessary. The homogeneity of participants’ characteristics between the 2 groups will be evaluated by independent *t*, chi-squared or Fisher exact tests, as appropriate. The generalized estimating equations (GEE) analysis with small-sample correction for sandwich variance estimate, which can be used to account for the small number of clusters in cluster randomized trial,^[37]^ will be used for comparing the primary and secondary outcomes between the 2 groups. The GEE analysis will be performed with the procedure GLIMMIX implemented in SAS release 9.4 (SAS Institute Inc., Cary, NC). All statistical tests involved are 2-sided, with the level of significance set at 0.05.

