### Sample size estimation

2.4

Sample size is estimated based on the primary outcome of the HPV vaccine uptake rate. Several studies have revealed the low uptake rate of HPV vaccine (<10%) in HK.^[20,28,29]^ We anticipate that our proposed MDL-SHPVP can double the uptake rate, and have therefore set this target to determine its effectiveness a priori. We used the power analysis software PASS 14 (NCSS, Kaysville, UT) to estimate that a sample size of 266 participants in the intervention and control groups will be required to achieve 80% power at a 2-sided 5% level of significance to detect a net difference of at least 10% in the uptake rate between the 2 groups, assuming that the rate is 10% for the control group. To allow for an attrition rate of up to 20%, a total of 666 participants with 333 in each group are needed. Furthermore, to account for clustering design, a variance inflation factor, namely the design effect, must be imposed.^[30]^ The design effect is given by 1 + (*m*–1)∗ICC, where *m* is the average cluster size and ICC is the intracluster correlation coefficient of the underlying outcome. A synthesis study revealed that the ICC tends to be small in primary care research, with a median of 0.005 and an inter-quartile range of 0.000 to 0.021.^[31]^ As we do not have empirical data to estimate the ICC for the outcome, we account for an ICC of up to 0.02. By this standard, a total of 18 schools with at least 140 female adolescents from each school will be required.

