### Cluster randomization

2.5

Randomization will be performed at the school level (cluster) rather than the individual participant level to avoid contamination between the intervention and control groups. Schools will be randomized to either the intervention or control group in a 1:1 ratio. All eligible adolescents recruited from the same school will be allocated to either the intervention or control group. Group allocation will be concealed from outcome assessors and the investigators, and performed according to a random sequence generated by an independent statistician using computer-based randomization.

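### The planned baseline tests treat participants as independent although schools are randomized, so their p-values will overstate imbalance whenever a characteristic clusters by school; the outcome analysis is not affected

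*Protocol article*

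**What the plan says.** The Data analysis section (2.10) of the protocol article states: "The homogeneity of participants’ characteristics between the 2 groups will be evaluated by independent *t*, chi-squared or Fisher exact tests, as appropriate". Categorical characteristics are thus to be compared by "chi-squared or Fisher exact tests, as appropriate", with no mention of clustering. The section then gives the clustering-aware method, GEE with a small-sample variance correction, a specific scope: it "will be used for comparing the primary and secondary outcomes between the 2 groups". The section ends with a general rule: "All statistical tests involved are 2-sided, with the level of significance set at 0.05". Read together, the baseline comparisons are formal tests with a declared 5% level, and the cluster adjustment does not extend to them.

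Elsewhere the article is clear that the design is clustered. Section 2.5 (Cluster randomization) says: "Randomization will be performed at the school level (cluster) rather than the individual participant level", and: "Schools will be randomized to either the intervention or control group in a 1:1 ratio". Section 2.4 (Sample size estimation) says that, "to account for clustering design, a variance inflation factor, namely the design effect, must be imposed", and concludes that "a total of 18 schools with at least 140 female adolescents from each school will be required".

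**The concern.** The independent t, chi-squared and Fisher exact tests all take each participant as a separate piece of information. When whole schools are allocated, an arm's mean or percentage carries between-school variation that these tests leave out of the standard error. Parental education, income and occupation, and adolescents' age and vaccination history, are among the characteristics that Section 2.8.5 collects, and any of them may differ between schools. For each one that does, the test rejects more often than the stated 5%, even when allocation has worked perfectly.

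At stake is how the baseline table is read. Small p-values that reflect ordinary differences between schools could be taken as evidence that the arms were not comparable. The article accounts for clustering in its sample size and its outcome analysis, so the baseline sentence is out of step with the rest of the plan.

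**Working it through.** **Inputs.** From Section 2.4: 18 schools, m = 140 girls per school, 666 participants before the clustering adjustment, design effect DE = 1 + (m − 1) × ICC, an ICC of up to 0.02 for vaccine uptake, and a cited ICC median of 0.005 with upper quartile 0.021. From Section 2.5: 1:1 allocation, so 9 schools against 9. From Section 2.10: two-sided 0.05. Assumed here, because the article gives no ICC for baseline characteristics: that the cited values, and 0.05 and 0.10, are plausible points to examine.

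**The plan's own figure first.**
- DE = 1 + 139 × 0.02 = 3.78.
- 666 × 3.78 = 2517.5, and 2517.5 / 140 = 17.98, rounded up to 18 schools.
- 18 × 140 = 2520, as stated. So the article's own planning implies a design effect of 3.78 for uptake.

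**False-positive rate of a test that ignores clustering.** The correct standard error is √DE times the one used, so a nominal two-sided 5% test has actual size 2 × [1 − Φ(1.96 / √DE)]. At baseline no attrition has occurred, so m = 140 applies.

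| ICC of the characteristic | Source | DE | 1.96/√DE | Actual size |
|---|---|---|---|---|
| 0 | cited lower quartile | 1.000 | 1.960 | 5.0% |
| 0.005 | cited median | 1.695 | 1.505 | 13.2% |
| 0.02 | planning value for uptake | 3.780 | 1.008 | 31.3% |
| 0.021 | cited upper quartile | 3.919 | 0.990 | 32.2% |
| 0.05 | assumed | 7.950 | 0.695 | 48.7% |
| 0.10 | assumed | 14.900 | 0.508 | 61.2% |

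**Check by simulation.** 6000 replicates with 9 against 9 schools of 140 and no true difference; the binary characteristic had 30% prevalence.
- ICC 0.005: t test 12.6%, chi-squared 12.8%.
- ICC 0.02: t test 31.9%, chi-squared 30.4%.
- ICC 0.05: t test 49.0%, chi-squared 47.8%.
- ICC 0.10: t test 61.1%, chi-squared 62.9%.
- A t test on the 18 school means rejected 4.6% to 5.1% of the time across the same ICCs.

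The formula and the simulation agree, and a simple cluster-level test restores the stated level. Fisher's exact test was not simulated.

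**The case against.** The strongest case against the point is that nothing turns on it, and most of that case stands. The article does not use the homogeneity tests to choose covariates, change the model or judge the randomization. The primary and secondary outcomes are compared by GEE, which handles clustering separately. A reader might infer that false imbalances will drive post hoc adjustment or weaken the trial's conclusions; the article plans nothing of the kind.

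A reader might also infer that about 31% of baseline characteristics will look imbalanced. That does not follow. The 0.02 is an upper planning value for uptake, adopted without empirical data, and is not an ICC for parental age or income. At the cited median the rate is 13%, and at an ICC of zero it is the nominal 5%. Nor can the rate be compounded over a list of characteristics to claim near-certain false findings: that would need independent characteristics, and education, occupation and income are plainly related.

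Finally, one might argue that baseline testing is pointless because any difference between randomized arms must be chance. That holds for schools, but the article does not fix whether participants are enrolled before or after their school is allocated, and eligibility includes a parent's readiness to come to education sessions. If enrolment follows allocation, recruitment could differ between arms, and comparing participants could be informative. That supports comparing the arms, but not with these tests, which would still mistake ordinary between-school variation for imbalance.

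The objection that an unseen analysis plan may supply the detail does not remove the point, because the article names the tests. A later document could only replace the sentence.

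**Conclusion.** The point holds as a minor error confined to the baseline comparison. The named tests cannot keep their declared 5% level for any characteristic with a positive ICC. With 140 girls per school, the false-positive rate per test is about 13% at an ICC of 0.005, about 31% at 0.02 and about 49% at 0.05. These figures assume equal school sizes and a large-sample approximation, which the simulation supports. They are conditional on ICCs that the documents do not give for baseline characteristics, so the actual excess is unknown and will differ between characteristics. The outcome inference is untouched.

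**What to change.** Replace the homogeneity sentence in Section 2.10. The replacement should say that baseline characteristics will be summarized by arm at both school and individual level, with means and standard deviations or counts and percentages, and without p-values; standardized differences can be added if wanted. If the investigators prefer to keep tests, the sentence should name a cluster-adjusted comparison, such as the small-sample-corrected GEE already planned for the outcomes or a test on school-level means.

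The cost is negligible: one sentence, no further data or participants, and little or no extra analysis work.

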### Patient and public involvement

2.11

User engagement will be promoted via user-centered design methods.^[38]^ Twenty-six potential users and key stakeholders, including 8 parents, 8 adolescents, 4 secondary school teachers, 2 school principals, 2 school nurses, and 2 social workers, will be engaged in the design of the MDL-SHPVP. Discovery interviews will be conducted to obtain a range of perspectives and insights and examine their perceived information needs, views of HPV vaccination, and program expectations. They will also be asked to review the deliverables, and a cycle of feedback loops will be initiated between them and the project team.

### Reporting guidelines

2.12

SPIRIT reporting guidelines were adhered in this protocol.^[39]^

## Ethics and dissemination

3

Ethical approval was obtained from the Joint Chinese University of Hong Kong-New Territories East Cluster Clinical Research Ethics Committee (Ref. no.: 2019.055) on March 13, 2019. We will protect participants’ rights and safety by adhering to local laws, the Hong Kong Personal Data (Privacy) Ordinance, the Declaration of Helsinki, institutional policies, and the ICH-GCP. Eligible schools and participants will receive an explanation of the project, potential risks or benefits, and their right to voluntary participation, withdrawal from the study at any time without negative consequences, and confidentiality. Informed consent will be obtained. Consent forms with the option of participation for parents/guardians will be sent home with adolescents. All information collected will be kept strictly confidential. Study findings will be disseminated via peer-reviewed publications and presentations at relevant events and conferences.

## Study timeline

4

The study will be conducted over a period of 30 months. Recruitment of participants is estimated to begin in December 2020 and will continue over 12 months. It will be followed with baseline measurement, intervention delivery, follow-up measurement, and results analysis, writing, and dissemination.
